### 2.14. Outcome Measures

#### 2.14.1. Primary Outcomes

The primary outcome for individuals with LRTIs will be measured through the beliefs about medicine questionnaire (BMQ), purely to observe the participant’s beliefs about AB [33]. The BMQ was developed on a pooled basis, and its items were derived from the already published literature and interviews with ill patients [33]. Alongside the primary outcomes, the participant’s knowledge of antibiotic use, and antibiotics’ resistance will be observed through the WHO public awareness surveys questionnaire (PAS-QA). A 37-item PAS-QA will include a demographics scale (1–8) and a main QA comprising the use of antibiotics (1–8), knowledge of antibiotics (9–10 (10.1–10.6), Q12, and Q13 Likert scale (1–8, 1–6) and Q13 (antibiotics use in agriculture) [34]. Both PAS-QA and BMQ will identify the level of understanding of antibiotics among the LRTIs patients and will be measured as the primary outcome.

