## Abstract

Globally, lower respiratory infections (LRTIs) are one of the most common infectious diseases whichaffect majority of the population and as a result of inappropriate antibiotics practices lead to antibiotic resistance (AR). An individual randomized control trial will be conducted in the post-conflict areas of Swat, Pakistan, through a random sampling method. Patients aged > 18 years will be recruited from five community pharmacies and assigned to equally sized groups to receive either pharmacist-led education interventions or usual care with no intervention. A total of 400 (control = 200, study = 200) patients will be included, with prescriptions comprised of antibiotics for LRTIs. The outcomes measured in both groups will be a combination of treatment cure rate and adherence, which will be assessed using the Morisky Medication Adherence Scale and pill count. The trial comprises pharmacist-led educational interventions to improve treatment outcomes for patients with LRTIs. This study might establish the groundwork for pharmaceutical care of LRTIs patients with antibacterial therapy and the future delivery of a care strategy for the improvement of LRTIs treatment outcomes in post-conflict, remote areas of the third world and LMICs.

**Trial registration**: Chinese Clinical Trials Registry, identifier: ChiCTR2000040453, registered on 28 November 2020.

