Nonetheless, antibiotics are still used for the treatment of LRTIs, resulting in the development of antimicrobial resistance [12,13]. Antimicrobials were originally regarded as lifesavers, with the best cure being antibiotics. However, incorrect antibiotic usage in the treatment of respiratory diseases might result in the emergence of resistance [14,15,16]. Antibiotics were misused in clinics because numerous isolates revealed high levels of antibiotic resistance; consequently, efficient antibiotic resistance surveillance is urgently needed to limit antibiotic abuse in China and Indonesia [17,18]. Treatment failure was more common in patients with RTIs in Pakistan because treatment outcomes are linked to antibiotic resistance [19].

Educational interventions could increase appropriate antibiotic prescription, dispensing, and/or use, which are commonly employed multimodal interventions [20,21,22]. Educational interventions at the community level reported a lower rate of antibiotic prescription, and enhanced knowledge of and attitudes towards antibiotic misuse [23]. Therefore, there has been no coverage of the topic, including educational interventions on patients recruited at community pharmacies, to improve adherence to antibiotic therapy in Pakistan. Hence, one of the barriers to care is the physical distance of rural communities from urban healthcare facilities. One of our baseline studies reported that the education of rural people is key to reducing the misuse of antibiotics [24].

The post-conflict areas (Swat) of Pakistan have witnessed extensive militancy since 2007. This has continued for many years, as the majority of the population of rural areas were displaced and migrated to the safest areas of the country [25]. During 2009, the people of Swat were asked to return after the area was cleared; however, the unremitting military presence and intermittent conflicts between security agencies and militants remain a social restiveness [26]. In the post-conflict areas of Swat, misuse of antibiotics occurs at a high frequency [24]. To address this gap, brief educational interventions will be delivered to the patients with LRTIs.

Therefore, this study aims to determine the adherence to prescribed antibiotics through educational interventions in post-conflict rural areas of Pakistan.

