## 2. Materials and Methods

### 2.1. Objectives and Hypothesis

The main objective of the current trial is to test the adherence to LRTI treatment in the local/rural villages of Swat, Pakistan. The secondary objective is to assess the improvements and the success rate of the therapy. First, the quantitative part will be completed; then, a qualitative interview will be conducted.

The primary hypothesis is; the intervention group will gain knowledge of, and adhere to, the prescribed therapy for LRTIs at a higher rate than the control group at 2 and 7 weeks. The secondary hypothesis is as follows.

Post-assessment will be conducted in the second week and endpoint evaluation at the end of seventh week; participants who received the intervention are expected to report positive changes in terms of their adherence to the medication and a reduction in antibiotic storage. After the seventh week, those in the intervention group are more likely to stick to their prescribed medication. Following the quantitative phase of the research, a qualitative assessment will be conducted to determine its acceptability.

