### 2.7. Sample Size

The previous literature will serve as a guide for calculating sample size, based on the effect of the prescribed antibiotics and pharmacist-led educational interventions on successful adherence to therapy [31,32]. A sample size of the responses will be required to give a 95% confidence interval with a 5% margin of error. Therefore, the maximum number patients from each pharmacy will be recruited until the study sample size surpasses both groups (control and interventions). Once the sample size is achieved, the principal investigator and team members will halt the patient recruitment. We will aim to achieve a 1:1 allocation ratio in the intervention or control groups, with 80%’ power and an alpha error of 5%. For the dropout participants, a 20% attrition rate will be supposed, resulting in a minimum sample size of 400 (200 in each group).

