#### 2.14.2. Secondary Outcomes

The measure of adherence to the prescribed therapy for LRTIs will be a secondary outcome. MMAS-8 combined the adherence endpoint scale and (% age) rate of pill count; this will be used to assess the AB adherence in LRTI patients. The first seven items of the MMAS-8 adherence scale must be answered with a yes or no (dichotomous) response, while the next five questions are on a Likert scale [35,36]. The Pills Count is a simple and unconventional way to examine a patient’s adherence to a specific medication [37]. The ability to evaluate the LRTI acceptance strategy is evidenced by the inclusion of the words “non-adherent” or “adherent” on previously circulating examinations. The present examination group showed that a patient finishing the initial trial is projected to have “disciple” with an MMAS-8 ≥ 6 and a pill count rate ≥ of 80% [35].

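### Adherence is the main objective and the basis of the sample size, but the outcome and analysis sections make two questionnaires primary and adherence secondary

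*Protocol article*

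**What the plan says.** Adherence as the purpose of the trial:

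- Introduction: "this study aims to determine the adherence to prescribed antibiotics through educational interventions in post-conflict rural areas of Pakistan".
- Section 2.1: "The main objective of the current trial is to test the adherence to LRTI treatment in the local/rural villages of Swat, Pakistan". The secondary objective there is therapy improvement and success, not adherence.
- Section 2.7: the sample size is guided by earlier literature on the effect of the prescribed antibiotics and "pharmacist-led educational interventions on successful adherence to therapy", with 80% power, 5% alpha, 20% attrition and 400 patients.
- Discussion: the overall goal is better adherence and less household storage of unused antibiotics.

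Adherence where the test is defined:

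- Section 2.14.1: "Both PAS-QA and BMQ will identify the level of understanding of antibiotics among the LRTIs patients and will be measured as the primary outcome".
- Section 2.14.2: "The measure of adherence to the prescribed therapy for LRTIs will be a secondary outcome".
- Section 2.17: the primary endpoint gets a linear mixed model with baseline BMQ and PAS-QA as covariates. Adherence is left to the secondary analysis.

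Two further statements fit neither ranking fully. The abstract says: "The outcomes measured in both groups will be a combination of treatment cure rate and adherence". The primary hypothesis in section 2.1 joins knowledge and adherence, both expected to be better "at a higher rate than the control group at 2 and 7 weeks".

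**The concern.** The primary outcome decides which result counts as the trial's answer and which endpoint the power statement must describe. Here those two roles fall on different variables. If the plan is followed as written, the trial could be reported as positive on questionnaire scores while adherence shows no difference, or as negative on the questionnaires while adherence improves. Either way, readers could not tell whether the main objective had been met. A later analysis plan cannot settle this while its parent protocol ranks the same outcome as both main and secondary.

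A lesser matter is that section 2.14.1 gives primary status to two instruments, section 2.1 names two time points, and section 2.17 derives a mean difference at each visit. The article does not say which of these results would count as success.

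**Working it through.** **1. The ranking, side by side**

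| Place | Endpoint given the leading role |
|---|---|
| Abstract | cure rate combined with adherence |
| Introduction, aim | adherence |
| 2.1, main objective | adherence |
| 2.1, primary hypothesis | knowledge and adherence |
| 2.7, sample size | adherence |
| 2.14.1, primary outcome | BMQ and PAS-QA |
| 2.14.2 | adherence, as secondary |
| 2.17, primary model | BMQ and PAS-QA |
| Discussion, goal | adherence and storage |

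The sections that fix the test (2.14, 2.17) disagree with those that fix the question and the power (Introduction, 2.1, 2.7). No reading of the current text makes all rows agree.

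**2. The stated sample size of 400**

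Inputs in section 2.7: 80% power, 5% alpha, 1:1 allocation, 20% attrition, and a 95% confidence interval with a 5% margin of error. No adherence rate, difference or questionnaire SD is given, so the power route cannot be reproduced.

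Precision route, with p = 0.5 assumed: n = 1.96² × 0.5 × 0.5 / 0.05² = 384.1, so 385. After attrition, 385 / 0.8 = 481.25, so 482. Neither figure is 400.

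**3. What 400 can detect on adherence**

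Evaluable per arm: 200 × (1 − 0.20) = 160. With two-sided 5% alpha (sidedness is my assumption) and independent participants,

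power = Φ{[Δ√n − 1.96√(2p̄(1 − p̄))] / √(p₁(1 − p₁) + p₂(1 − p₂))}, where p̄ is the mean of the two rates.

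Solving for 80% power at n = 160:

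| Assumed control rate | Detectable difference (points) |
|---|---|
| 30% | 15.2 |
| 40% | 15.6 |
| 50% | 15.5 |
| 60% | 14.7 |
| 70% | 13.3 |
| 80% | 11.0 |

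For example, 50% versus 65.5% needs 159 evaluable per arm, and 159 / 0.8 gives 199 enrolled, close to the stated 200. By contrast, 50% versus 60% has power of only 0.44 at 160 per arm. It would need 388 evaluable, or 388 / 0.8 = 485 enrolled, per arm.

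**4. What 400 can detect on a questionnaire score**

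Standardized difference = (1.96 + 0.842) × √(2/160) = 0.31. If alpha were split over BMQ and PAS-QA, (2.241 + 0.842) × √(2/160) = 0.34. Section 2.7 contains nothing that links 400 to either figure.

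**5. Type I error, only if any one success suffices**

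- Two independent tests (two instruments, one visit): 1 − 0.95² = 0.0975.
- Four independent tests (two instruments, two visits): 1 − 0.95⁴ = 0.185.
- Four correlated tests, simulated: about 0.16 with correlation 0.3 between instruments and 0.6 between visits, and about 0.13 with all correlations 0.7. These correlations are assumptions with no source in the article.

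**The case against.** The strongest defence is that knowledge is part of the trial's question. The primary hypothesis names it, section 2.5.2 makes week 7 the assessment of overall knowledge, and section 2.17 bases the primary analysis on education. That stands. A reader might infer that the planned test misses the trial's question altogether, but the text does not support this, because PAS-QA addresses the knowledge part. Nor is BMQ shown to be irrelevant. Section 2.14.1 limits it to beliefs in one sentence and credits it with measuring understanding in another, which is an ambiguity. What remains is that neither instrument measures adherence.

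A reader might also infer that the 5% alpha is already lost. The article does not say that either questionnaire suffices. If both had to succeed at one visit, the error could not exceed 5%. Section 2.1 calls week 2 a post-assessment and week 7 the endpoint evaluation, so reporting a difference at each visit does not make each one a primary test. Section 2.17 also promises detailed statistical plans, and a testing order is commonly placed there. The inflation is therefore conditional.

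Finally, a reader might take Table 2 as listing cure as an outcome. Its row is therapy success rate, which section 2.5.2 ties to the rate of adherence, so that reading is not secure. None of this removes the conflict over which outcome is primary.

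**Conclusion.** The concern holds as a contradiction within the current text, and it must be fixed. The primary analysis answers at most the knowledge part of the primary hypothesis and leaves the main objective to a secondary analysis. The stated 80% power belongs in words to adherence, while the confirmatory model tests questionnaire scores. This conclusion rests on the wording alone and does not depend on any assumed figure.

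The sizes do depend on assumptions. The detectable adherence difference of about 11 to 16 points assumes control rates of 30% to 80%, a two-sided 5% test, 160 evaluable per arm and independent participants. The error rates of 9.75% and 18.5% assume independent tests and a rule that any single success counts. The failure to reproduce 400 shows that its inputs are not stated, not that the number is wrong.

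**What to change.** - **Section 2.14:** name adherence as the single primary outcome, using the composite in section 2.14.2 (MMAS-8 of at least 6 and pill count of at least 80%), at one stated time point. The start of week 2 is one option, since sections 2.5.2 and 2.11 check adherence and the antibiotics then. Section 2.1 calls week 7 the endpoint evaluation, so the two must be reconciled. Restate the MMAS-8 description at the same time: seven yes/no items followed by five more do not fit a scale named for eight. Move BMQ and PAS-QA to secondary.
- **Section 2.17:** analyse the composite with a logistic model adjusted for baseline values already collected, and report a risk difference with its 95% confidence interval. Keep the linear mixed model for the questionnaires.
- **Section 2.7:** state the control and intervention adherence rates assumed, and show that they lead to 400 after attrition.
- **Abstract, 2.1, 2.14 and 2.17:** align them, and say where therapy success and antibiotic storage stand, since neither has an entry in section 2.14.

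If the sponsor prefers the questionnaires as primary, then the aim, main objective, abstract and sample-size basis must change instead, with a success rule for the two instruments.

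The cost is mostly wording. The composite is already to be collected, though storage may need a question and therapy success a definition. The questionnaires lose primary status, and the detectable adherence difference must be stated openly. If the sponsor considers about 11 to 16 points too optimistic, the sample size has to be reopened.

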#### 2.14.2. Secondary Outcomes

The measure of adherence to the prescribed therapy for LRTIs will be a secondary outcome. MMAS-8 combined the adherence endpoint scale and (% age) rate of pill count; this will be used to assess the AB adherence in LRTI patients. The first seven items of the MMAS-8 adherence scale must be answered with a yes or no (dichotomous) response, while the next five questions are on a Likert scale [35,36]. The Pills Count is a simple and unconventional way to examine a patient’s adherence to a specific medication [37]. The ability to evaluate the LRTI acceptance strategy is evidenced by the inclusion of the words “non-adherent” or “adherent” on previously circulating examinations. The present examination group showed that a patient finishing the initial trial is projected to have “disciple” with an MMAS-8 ≥ 6 and a pill count rate ≥ of 80% [35].

### 2.15. Qualitative Evaluation

The trial team will conduct over 20 semi-structured interviews with a random subset of participants. The trial will include individuals with same number of dropouts and completers, and a semi-structured interviewing guide that covers a topic relevant to each respondent category. Through a mobile phone call, all interviews will be recorded (audio) through a mobile phone recorder with prior consent [38,39]. To avoid bias in the responses, the intervention teams will undertake an independent analysis of the collected qualitative interviews. Hence, the final analysis will be conducted manually, following a predetermined thematic analysis approach [38,39,40]. The schedule for the structured interviews will be finalized for each participant as per feasibility and ease, and will stop at the saturation point.

### 2.16. Trial Data Management

Data will be managed per established norms. Monitoring will be required at all stages to gather true, authentic, and verified data. Every day, the principal investigator’s field office will save the data on a paper evaluation study booklet with a participant’s given codes. The data will be checked by the lead investigator, with all highlighted queries being rectified as soon as possible, and any discrepancies being resolved by a third data entry person. Following the creation of electronic files, all data will be password-protected, and only authorized individuals will have access to the database, which will be backed up every day. The participant’s information will remain confidential to maintain quality and data secrecy. Only pharmacists will be aware of the private information in the intervention; all data forms will be kept in closed filing cabinets. The trial team will monitor the trial progress on a daily basis.

### 2.17. Statistical Analysis Methods

According to the Consolidated Standards of Reporting Trials (CONSORT) for RCTs, all the findings will be reported as per the given guidelines [41]. Data will be analyzed through IBM-SPSS-Statistics (version 21) and STATA (version 11). The basis of primary analysis is to educate the population with LRTIs, and the secondary analysis will be based on the adherence rate and behavior of the population. For the primary endpoint analysis, a linear mixed model will be employed. The mixed model will include the visits, interactions with the treatment group, and baseline measurement of BMQ and PAS-QA as covariates, and subjects as a random effect. The mean differences (MD) between the two arms at each visit, with a confidence interval (CI 95%), will be derived from a generalized mixed model, along with each visit from the treatment arm. Before unmasking the trial, all analyses will be defined in detail with their assigned statistical plans.

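### Fitted as written, the primary mixed model implies equal variance at weeks 2 and 7; an unstructured covariance would protect the by-visit confidence intervals at almost no cost

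*Protocol article*

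**What the plan says.** Section 2.17 of the protocol article names the model type: "For the primary endpoint analysis, a linear mixed model will be employed". Its terms are visits, interactions with treatment group, and "baseline measurement of BMQ and PAS-QA as covariates, and subjects as a random effect". No other random term is named, and no residual covariance is described.

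The output required is "The mean differences (MD) between the two arms at each visit", with 95% confidence intervals. The same sentence says that these differences "will be derived from a generalized mixed model, along with each visit from the treatment arm", although the model named just before is a linear one.

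The section closes by deferring detail: "Before unmasking the trial, all analyses will be defined in detail with their assigned statistical plans".

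Section 2.1 sets the comparison times. The intervention group is expected to do better "at a higher rate than the control group at 2 and 7 weeks". That makes two post-baseline assessments, with baseline entering as a covariate.

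**The concern.** A random subject effect with a single residual variance makes the variance at each visit the sum of the same two components. Each by-visit confidence interval then rests on a variance averaged over the visits, not on that visit's own. If the spread is constant, nothing is lost. If it is not, the interval is too narrow at the more variable visit and too wide at the other. The nominal 5% error rate is exceeded at the first, and power is given away at the second.

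Constant spread cannot be taken for granted here. Section 2.5.1 gives the full intervention at time zero. Section 2.5.2 then plans further calls between the two assessments, meant to raise knowledge, and Section 2.14.1 makes knowledge (PAS-QA) part of the primary outcome. The intervention therefore keeps acting on the outcome between its two measurements.

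Separately, the text gives two names to the model that supplies the differences. If a reader took generalized to mean a non-identity link, the output would not be a mean difference.

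**Working it through.** The point disputes no figure printed in the plan, so there is none to reproduce. The check asks how far the by-visit intervals move if the two visits have different SDs.

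**Inputs from the article**
- Two post-baseline visits, weeks 2 and 7 (Section 2.1).
- 200 patients per arm, 1:1 allocation, 20% attrition, 5% alpha (Section 2.7; two-sided is assumed).
- Visit, arm-by-visit and baseline terms, with subject as the random effect (Section 2.17).

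**Assumptions, because the article gives no values**
- Ratio r of the larger to the smaller visit SD: 1.0 to 1.5.
- For the simulation, a residual correlation of 0.5 between visits, and all of the 20% attrition at the second visit, which is also the more variable one.

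**Step 1: what the model implies.** With subject variance σu² and residual variance σe², each visit has variance σu² + σe² and the covariance between visits is σu². With two visits there is only one correlation, so the only restriction that can matter here is equal variance.

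**Step 2: approximate coverage.** Set the smaller SD to 1 and the larger to r. The model uses a pooled SD of √((1 + r²)/2). Coverage of a nominal 95% interval at a visit with SD s is 2Φ(1.96 × pooled SD / s) − 1.

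For r = 1.25 the pooled SD is √((1 + 1.5625)/2) = 1.132. At the more variable visit the interval has 1.132/1.25 = 0.906 of its correct width, and coverage is 92.4%. At the other visit it is 1.132 times the correct width, and coverage is 97.3%.

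| SD ratio | Width, more variable visit | Coverage, more variable visit | Width, other visit | Coverage, other visit |
|---|---|---|---|---|
| 1.0 | 1.000 | 95.0% | 1.000 | 95.0% |
| 1.1 | 0.956 | 93.9% | 1.051 | 96.1% |
| 1.25 | 0.906 | 92.4% | 1.132 | 97.3% |
| 1.5 | 0.850 | 90.4% | 1.275 | 98.8% |

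**Step 3: simulation.** There were 1000 runs per ratio with REML fitting, 200 patients per arm, a baseline covariate and visit-by-arm terms. The Monte Carlo standard error near 95% is √(0.95 × 0.05/1000), about 0.7 points.

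| SD ratio | Random intercept: more variable / other | Unstructured: more variable / other |
|---|---|---|
| 1.0 (second / first visit) | 95.4% / 95.2% | 95.2% / 95.2% |
| 1.25 | 92.6% / 97.1% | 95.5% / 94.7% |
| 1.5 | 90.0% / 98.4% | 95.0% / 94.9% |

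The simulation agrees with the approximation. The unstructured covariance held about 95% at both visits and lost no coverage when the SDs were equal.

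**Step 4: the two model names.** A generalized mixed model with identity link and normal errors is the linear mixed model. Section 2.17 asks for mean differences and mentions no other link. The two sentences can therefore be reconciled, but the text should name one model.

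**The case against.** The strongest reply is that the article does not commit the error. Section 2.17 is silent on the residual covariance. A subject random effect can sit alongside visit-specific residual variances or robust standard errors. Residual structure is usual content for a statistical analysis plan, and the section says that such plans will define the analyses before unmasking. This stands, and it is why the point is not put as a mistake in the protocol.

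A reader might also infer that the model imposes a single correlation on all visits. The documents do not support that as a defect. With weeks 2 and 7 and baseline as a covariate there is one between-visit correlation and nothing to constrain. It would matter only if the primary outcome were also measured at other weeks. Section 2.5.2 describes the intermediate calls as educational, and the primary-outcome row of Table 2 is blank as extracted.

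It is also fair to object that no figure in the article shows the spread changing, in either direction, and that a 10% change in SD moves coverage by only about one point. Both stand. The harm is conditional, and which visit suffers depends on which has the larger SD.

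Finally, the word generalized may be no more than loose wording. That is accepted: it is a wording inconsistency and does not show that a non-identity link was meant.

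What survives is narrower. The only covariance ingredient the text names, fitted in its ordinary sense, implies equal variances. A safer choice is available at negligible cost for exactly the by-visit results that the plan wants.

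**Conclusion.** The point holds as an improvement at almost no cost, not as a demonstrated error. The primary model as worded implies equal variance at weeks 2 and 7. If the SDs differ by a factor of 1.1, 1.25 or 1.5, the nominal 95% interval covers about 94%, 92.5% or 90% at the more variable visit, and about 96%, 97% or 98.5% at the other.

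These figures rest on the assumed SD ratios, on two post-baseline visits, and on a random intercept with one residual variance and no robust standard errors. A reader might conclude that the trial's primary intervals will be wrong. The article does not support that: it gives no visit SDs, does not state the residual structure, and leaves detail to a later plan.

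**What to change.** In the statistical analysis plan, before unmasking:

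- Keep the fixed effects already stated in Section 2.17: visit, its interaction with treatment group, and the baseline measurements.
- Replace the subject random effect by an unstructured within-subject covariance across the post-baseline visits, fitted by REML.
- State that the by-visit mean differences and their 95% confidence intervals come from this same linear mixed model, and correct the reference to a generalized mixed model.

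The cost is one model statement. For two visits the covariance has 3 parameters (two variances and one covariance), against 2 for the random intercept, with 400 patients planned. In the simulation there was no coverage penalty when the variances were equal.
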